### Blinding

Due to the limitations of this protocol and the nature of acupuncture treatment, the acupuncturists participating in this trial could not be blinded to the assignments, the patients were blinded. Patients were informed that they will be randomized to receive one of two effective interventions after registration. Every patient knew the type of treatment they received, but they did not know another type. Each patient's acupuncture intervention was carried out in a separate personal space and at different times to avoid communication between patients. The distribution of patient groups by data managers and statisticians was not clear. Experts, data managers, and statisticians were not allowed to communicate with others about patients' treatment, so as to improve the accuracy of test indicators and ensure the effectiveness of interventions and the objectivity and reliability of the evaluation. The blind method was made public after the statistical analysis was completed.

### Inclusion and Exclusion Criteria

Inclusion Criteria. The Eligible Participants Should Meet all of the Following Criteria:

(1) The patients met the diagnostic criteria of ischemic stroke and were diagnosed by computed tomography (CT) or magnetic resonance imaging (MRI).

(2) Patients with clinical symptoms of paralysis on one side of the limb and upper extremity motor dysfunction.

(3) Patients with the MAS is the grade I and above, grade III and below.

(4) Men or women with an age range between 20 and 70 years.

(5) The Brunnstrom recovery stage (BRS) of the patient's upper extremity ranged from II to IV.

(6) Patients who are stable, conscious, and have no communication problems.

(7) Patients with no previous history of upper extremity dysfunction, first onset, or legacy of stroke.

(8) The participants were voluntary and signed the relevant informed consent.

Exclusion Criteria. Criteria for Exclusion Are the Following:

(1) Patients with upper extremity motor dysfunction, combined with severe cardiovascular disease, hypertension, respiratory infection, severe renal dysfunction, severe diabetes mellitus, and a history of psychiatric, were accompanied by agnosia, apraxia, and an intellectual disability that affects communication and evaluation.

(2) Patients with unstable vital signs in the acute phase.

(3) Patients in thrombolytic therapy.

(4) Fear of acupuncture and poor physical fitness, such as easy to faint, are not suitable for acupuncture treatment of patients.

(5) Patients who have taken sedative drugs and muscle relaxants in the recent past.

(6) Patients with transient ischemic attack (TIA), reversible ischemic neurological deficits, subarachnoid hemorrhage, etc.

(7) Patients who are pregnant, lactating, or preparing for pregnancy.

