### Randomization

Eligible patients were allocated, in a 1:1 ratio were randomly assigned to the experimental group or the control group, following the randomization principle, which employs block randomization to generate random-number sequence using the SPSS, and an independent statistician who did not participate in the treatment and result evaluation was responsible for processing the results. Meanwhile, we also prepared sealed opaque envelopes with group information strips in these envelopes, which was hidden until the informed consent was obtained.

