#### Primary Outcomes

The main result is the MAS, which is the most widely used clinical spasm scale (32). It is usually used to obtain the baseline evaluation of increased muscle tone, monitor the course of the disease, determine the effectiveness of drugs, and rehabilitation interventions, so as to reduce the overall increase of muscle tension, normalize the muscle tone of the selected muscle group, and guide physical therapy and other treatment decisions. It has the advantages of simplicity, time saving, and convenient operation. It is divided into 6 levels, i.e., 0, I, I +, II, III, and IV. Scoring methods, i.e., 0, 1, 2, 3, 4, and 5 points, represent 0, I, I +, II, III, and IV, respectively. The higher the MAS score, the more serious the spasticity. Compared with the lower limbs, the reliability of the upper limbs is better (33). The specific contents of MAS are shown in Table 3.

**Table 3 T3:** The modified Ashworth score (MAS)-specific scoring rules.

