### Statistical Analysis

After all the experimental data are verified to be correct, SPSS19.0 statistical software is used for statistical analysis. Classified variables will be analyzed using Pearson's χ^2^ test or Fisher's exact test, and continuous variables will be evaluated using Student's *t*-test or an appropriate non-parametric method. The statistical results are measured by the mean ± standard deviation (SD; *x* ± s); when comparing within or between groups, tests for normality and homogeneity of variance are performed prior to data analysis for each group. If the data satisfy normal distribution and homogeneity of variance, the *t*-test will be used for comparisons between two groups, and the least significant different (LSD) or Student-Newman-Keuls (SNK) method will be used for multiple comparisons. Instead, the rank-sum test will be used for non-normality or non-uniformity of variance. Set the test level as 0.05, *p* < 0.05, and the difference was statistically significant.

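### Brunnstrom stage and baseline MAS are known at entry, but the stated MAS comparison is unadjusted and may give up some precision

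*Protocol article*

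**What the plan says.** All places are in the protocol article.

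- **Entry.** Inclusion criterion 5 reads "The Brunnstrom recovery stage (BRS) of the patient's upper extremity ranged from II to IV". Criterion 3 reads "Patients with the MAS is the grade I and above, grade III and below", which on the article's 0 to 5 scoring means entry scores of 1 to 4. Neither criterion can be applied without rating the patient at screening.
- **Schedule.** Table 1 places the MAS at week 0 and again at week 4.
- **Outcome.** The Primary Outcomes section makes the MAS the main result and gives its direction: "The higher the MAS score, the more serious the spasticity".
- **Allocation.** The Randomization section describes a 1:1 scheme that "employs block randomization to generate random-number sequence using the SPSS". It names no stratification factor.
- **Analysis.** The Statistical Analysis section says that, under normality and equal variances, "the *t*-test will be used for comparisons between two groups"; otherwise a rank-sum test is used. It names no baseline term and does not say whether the week 4 score or the change from baseline is compared.

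**The concern.** Two gradings that could plausibly predict the week 4 MAS are available before treatment. On the text shown, neither is used in allocation or in the primary test. Plain blocks balance the number of patients per arm, not the mix of stages. If MAS change differs by entry stage, that difference stays in the residual variance of an unadjusted comparison. The standard error is then larger than it need be, and power is lost that a covariate would recover. At stake is the precision of the primary result, not its validity.

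**Working it through.** **The plan's own figure.** The Sample Size section gives 49 per group. Its printed formula with P = 0.65, quantiles 1.645 and 1.282, and δ = 0.20 gives 0.65 × 0.35 × (2.927/0.20)² = 48.7, so 49; 49 × 1.1 = 53.9, so 54. This figure rests on effective rates (65% and 85%) and does not involve stage or a MAS standard deviation. I use it here only for the number per arm.

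**Assumptions (none is in the documents).** One third of patients in each of stages II, III and IV. Within-stage SD of MAS change 0.8. Mean 4-week change apart from treatment of +d, 0 and −d in the three stages. The sign does not matter for the arithmetic, only the spread of the stage means. The treatment effect is set so that 49 per arm has 90% power (two-sided 5%) when d = 0: (1.96 + 1.2816) × 0.8 × √(2/49) = 0.524 points.

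**Formulas.**
- Between-stage variance = (2/3)d².
- Share explained by stage = (2/3)d² / (0.64 + (2/3)d²).
- Reduction in standard error from adjustment = 1 − √(0.64 / (0.64 + (2/3)d²)).
- Unadjusted power ≈ Φ(0.524 / SE − 1.96), with SE = √((0.64 + (2/3)d²) × 2/49).

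| d | Between-stage variance | Share explained | SE reduction | Unadjusted power | Power with stage in the model (simulated) |
|---|---|---|---|---|---|
| 0 | 0 | 0% | 0% | 0.90 | 0.885 |
| 0.25 | 0.042 | 0.042/0.682 = 6% | 3% | 0.88 | 0.886 |
| 0.5 | 0.167 | 0.167/0.807 = 21% | 11% | 0.82 | 0.896 |
| 0.75 (stress case) | 0.375 | 0.375/1.015 = 37% | 21% | 0.73 | 0.890 |

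The last column comes from 4,000 simulated trials per row, with blocks of 4 and 49 per arm. Its Monte Carlo error is about √(0.89 × 0.11/4000) = 0.005, so the four entries are practically the same. Unadjusted power in the same simulations was 0.891, 0.877, 0.820 and 0.725, in line with the formula.

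**In patients.** At d = 0.5, 49 unadjusted patients per arm carry the information of 49 × 0.64/0.807 = 39 adjusted ones. At d = 0.25 the figure is 49 × 0.64/0.682 = 46.

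**Validity.** With no treatment effect, the unadjusted and adjusted tests rejected in 0.047 to 0.053 of trials for every d. With a true effect of −0.524, the mean unadjusted estimate lay between −0.524 and −0.529. Neither shows bias or an inflated error rate.

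**Chance imbalance in one trial.** With 54 per arm and equal thirds, the SD of the difference in stage II share is √(2 × (1/3)(2/3)/54) = 0.091. A gap of 10 points or more, in either direction, then arises in about 27% of trials (normal approximation; 26% by simulation). Moving 10 points of share from stage IV to stage II shifts the mean difference by 0.1 × 2d, which is 0.05 points at d = 0.25 and 0.10 at d = 0.5. The unadjusted standard error at 54 per arm and d = 0.5 is √(0.807 × 2/54) = 0.17, so a shift of that size lies well inside ordinary sampling error, which already includes it.

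**The case against.** **The premise is outside the documents.** A reader who knows the Brunnstrom stages might infer that tone naturally rises from stage II and falls from stage IV, so that one MAS change means opposite things in different patients. The article neither defines the stages nor links them to a direction of tone. Criterion 3 also means that every patient, stage II included, enters with raised tone. The inference cannot be stated as fact. What stands is conditional: if stage predicts MAS change, precision is lost.

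**Bias.** A reader might infer that a chance excess of one stage makes an arm look worse whatever the treatment does. The documents do not support that. Allocation is randomised and concurrent, so any stage trend falls on both arms alike in expectation, and the simulated error rate and estimate bear this out. This objection stands in full.

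**Direction of the MAS.** The sentence on higher scores gives the direction of a spasticity scale; it does not define benefit for each patient. Motor function is measured separately by the FMA-UE. This stands too.

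**Stratification and time since stroke.** One might go further and ask for stratified envelopes and a time-since-onset factor. Unstratified blocks are a legitimate choice, and changing allocation during recruitment is hard to justify for a gain of this size when the model recovers it. Criteria on timing may sit in the full protocol; the article's wording on phase is "Patients with unstable vital signs in the acute phase". Table 1 lists medical history but does not show that onset time is recorded.

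**Detail left to the SAP.** Covariates are often specified there, and it is not shown. This limits the point, but the article does not stay silent: it names a specific unadjusted test. If the SAP already replaces it with an adjusted model, the point falls away.

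**Conclusion.** The point holds as a modest matter of efficiency. The stated primary comparison uses neither baseline MAS nor a stage grading that must already be rated at screening. It is valid and unbiased on average. If stage predicts MAS change, adjustment would cut the standard error by about 3% (d = 0.25) to 11% (d = 0.5). Unadjusted power would then be about 0.88 to 0.82, against about 0.89 to 0.90 adjusted. If stage predicts nothing, nothing material is lost either way.

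These figures rest on the assumed SD of 0.8, equal thirds and drift range, and on analysing change in MAS. They concern stage alone. The further gain from baseline MAS is not quantified, and if baseline MAS and stage overlap, stage will add less than shown. Severity is low, and confidence in the size is low.

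**What to change.** Before unblinding, prespecify the primary MAS comparison as one model with treatment, baseline MAS (the pre-treatment value) and screening Brunnstrom stage. Either ANCOVA on the week 4 score or an ordinal model would serve. The ordinal model suits a six-level scale and is the closer companion to the rank-sum test; ANCOVA reports a difference in points. Name one as primary in advance, and keep the t-test or rank-sum test, if wanted, as a sensitivity analysis.

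The cost is one or two extra model terms and a sentence in the analysis section, with no new visit or measurement. With no drift at all, simulated power was 0.885 adjusted against 0.891 unadjusted. The rated stage needs to be kept on the case report form, since Table 1 does not list it as a separate item. The ongoing allocation should stay as it is.

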#### Secondary Outcomes

The FMA-UE, CSS, and MBI were secondary outcome indicators.

The FMA-UE is often a widely used evaluation tool for evaluating upper extremity motor function during stroke rehabilitation. It can effectively, stably, and sensitively reflect the changes in patients' dysfunction with good reliability and validity (34, 35). Evaluate the flexion, coordination, range of motion, stability, and coordination of each joint of the patient's upper limb, which is composed of 33 items in four parts: hand, wrist, elbow, and shoulder, with a total score of 66. The lower the score, the more serious the upper extremity dysfunction. The minimum clinically important difference (MCID) of FMA-UE was 4.25–7.25 points (36). That is, if the difference in upper extremity motor function score before and after treatment is >MCID, it is considered that the upper extremity motor function of the patient has been improved, the treatment is effective and can surpass the random error (37).

The CSS was determined by the “Fourth National Conference on Cerebrovascular Diseases” (1995), which is mainly to evaluate the curative effect and is divided into basic cure (the score of functional defect was decreased by 91–100%, and the degree of disability was grade 0), significant effect (the score of functional defect was decreased by 46–90%, and the degree of disability was grade 1), improvement (the functional defect score was decreased by 18–45%), and ineffective (the functional defect score decreased by about 17%). The score is simple and easy to use (38).

The MBI is a standard scale that is widely used to evaluate the dysfunction of basic activities of daily living, which consists of 10 daily life activities, such as bathing, toilet, eating, and dressing, with a total score of 100. The higher the score, the better the self-care ability in daily life (39).

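### Inclusion (7) can be read to bar or to admit first-onset and sequelae patients, time since stroke is unbounded, and a within-patient FMA-UE gain is then taken as showing efficacy

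*Protocol article*

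**What the plan says.** In the Protocol article, the inclusion list under Inclusion and Exclusion Criteria opens with "The Eligible Participants Should Meet all of the Following Criteria", so each item is mandatory. Item (7) is "Patients with no previous history of upper extremity dysfunction, first onset, or legacy of stroke".

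These items bear on how far the patient is from the stroke:
- Inclusion (3): "Patients with the MAS is the grade I and above, grade III and below".
- Inclusion (5): "The Brunnstrom recovery stage (BRS) of the patient's upper extremity ranged from II to IV".
- Inclusion (6): "Patients who are stable, conscious, and have no communication problems".
- Exclusion (2): "Patients with unstable vital signs in the acute phase".
- Exclusion (3): "Patients in thrombolytic therapy".

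None gives a minimum or maximum number of days, weeks or months since onset, and the Elimination Criteria add none. The Randomization section describes 1:1 block randomisation and names no stratification factor.

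Secondary Outcomes gives the FMA-UE an MCID of 4.25–7.25 points. When a patient's before-after difference exceeds it, "it is considered that the upper extremity motor function of the patient has been improved, the treatment is effective and can surpass the random error". Statistical Analysis provides for comparisons both within and between groups. Under Interventions, both arms receive acupuncture on top of routine rehabilitation for 4 weeks.

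**The concern.** There are two linked problems.

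The first is who is in the trial. A mandatory criterion that can be read in opposite ways cannot be applied reproducibly by screeners, and a reader cannot tell to whom the result applies. With no bound on time since stroke, the remaining criteria do not settle this.

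The second is what is inferred from the patients enrolled. If some are still recovering on their own, part of their 4-week gain would have occurred anyway, and routine rehabilitation adds to it in both arms. A rule that reads an individual's gain as evidence for the treatment credits all of this to acupuncture. The same holds for a before-after test within one arm. Neither arm goes without acupuncture and rehabilitation, so no group shows what change would have occurred without them.

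**Working it through.** **Step 1: readings of Inclusion (7).** The sentence has one negation, three items and a final *or*.

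| Patient | Negation covers all three items | Negation covers only the first item | Likely intent: first-ever stroke, no earlier arm deficit |
|---|---|---|---|
| First stroke, no earlier arm problem | barred | admitted | admitted |
| First stroke long ago, now with sequelae | barred | admitted | admitted, as no time limit is given |
| Second stroke, first left no deficit | the only type left | not described by either remaining item | barred |

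The first two readings disagree on every row. The third is plausible, but needs the negation moved and the *or* replaced. No other criterion decides between them.

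**Step 2: limits on time since stroke.** Inclusions (3) and (5) restrict spasticity grade and recovery stage; Inclusion (6) and Exclusions (2) and (3) restrict clinical state. They narrow the range indirectly: an early patient enters only if stable and already at MAS I or above and Brunnstrom II or above. A patient meeting them soon after onset and one meeting them years later are both eligible.

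**Step 3: what mixing does to each kind of comparison.** The article gives no figure for natural recovery, so the inputs below are assumptions, shown as a range. Only the 54 per arm comes from the article (Trial Design and Setting; Sample Size). The outcome is a generic continuous change score with within-phase SD 1. A share p of patients are early (0.3 or 0.5) and gain g SD more than the others (0.5 or 1.0); the others gain nothing on average, and treatment does nothing. Each setting was simulated 20,000 times.

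- SD of the mixed population = √(1 + g²p(1−p)).
- One-arm before-after signal = p·g ÷ (SD/√54).

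| p | g | SD | One-arm signal | One-arm test significant | Between-arm test significant |
|---|---|---|---|---|---|
| 0.3 | 0.5 | 1.026 | 0.15 ÷ (1.026/7.348) = 1.07 | 19% | 5.0% |
| 0.3 | 1.0 | 1.100 | 0.30 ÷ (1.100/7.348) = 2.00 | 50% | 4.8% |
| 0.5 | 0.5 | 1.031 | 0.25 ÷ (1.031/7.348) = 1.78 | 42% | 5.1% |
| 0.5 | 1.0 | 1.118 | 0.50 ÷ (1.118/7.348) = 3.29 | 90% | 4.9% |

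The mean between-arm difference was about 0 in all four settings.

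**Step 4: cost to the between-arm comparison.** The SD rises by about 3% to 12%. The chance difference between arms in the early share has SD √(2p(1−p)/54):
- p = 0.3: √(0.42/54) = 0.088, 95% range ±17 percentage points.
- p = 0.5: √(0.50/54) = 0.096, 95% range ±19 percentage points.

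This imbalance averages to zero over trials and is already covered by the test's error rate.

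**The case against.** A reader might infer that spontaneous recovery will be mistaken for the effect of functional acupuncture in the trial as a whole. The documents do not support that. Trial Design and Setting makes efficacy a comparison of experimental with control group, allocation is random, and both arms are observed over the same 4 weeks. Natural recovery is balanced in expectation, and Step 3 shows the between-arm error rate staying near 5%.

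A reader might also infer that Inclusion (7) definitely excludes first strokes, or that nothing else in the criteria touches stroke phase. The first is one literal reading, probably unintended. The second is wrong, given Inclusions (3), (5) and (6) and Exclusions (2) and (3).

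It can fairly be added that the MCID sentence concerns a secondary scale, that no FMA-UE responder analysis is written into Statistical Analysis, and that Sample Size does not tie its 65% and 85% effective rates to this MCID. There is thus no documented route from the sentence to the main result. A time-since-stroke covariate is commonly left to an analysis plan, and its absence here is no fault. The full protocol (V2.0, cited under Trial Status) may word the criterion better.

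All of this limits the point without removing it. The criterion is printed, numbered and mandatory, and cannot be applied as it stands. The MCID sentence is a stated rule of interpretation, and it is wrong in a two-arm trial with rehabilitation in both arms, whatever the mix of stroke phases.

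**Conclusion.** The point holds in a limited form. Inclusion (7) does not define the stroke history required, and time since stroke is bounded only indirectly, so the target population is poorly specified. The rule reading an individual FMA-UE gain above the MCID as efficacy, and any within-group test used in the same way, cannot separate treatment from natural recovery or rehabilitation. Under the assumed range, an inert treatment gives a significant one-arm result in 19–90% of trials.

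The randomised comparison is not biased. Under the same assumptions it loses a little precision (SD up by about 3–12%) and carries ordinary chance imbalance. These figures rest on the assumed share and size of early recovery and on a generic continuous score; they are not estimates for the MAS. The ambiguity and the faulty inference depend on none of them.

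**What to change.** 1. Replace Inclusion (7) with separate statements: one giving the intended stroke history (first-ever stroke only, or earlier strokes allowed and on what condition), and one requiring no upper-limb dysfunction before the present stroke. The choice is the sponsor's. As recruitment began on 1 September 2021, also state which reading has been applied so far.
2. Report the range of time since stroke among enrolled patients. A new eligibility window during recruitment is not recommended here: applied only to later patients, it would put two eligibility regimes in one trial.
3. Remove the inference from an individual FMA-UE gain to effectiveness and judge efficacy only by the between-arm difference. If the proportion of patients exceeding the MCID is reported, compare it between arms, with one stated threshold in place of the range 4.25–7.25. Within-group changes can stay as description.
4. Prespecify adjustment of the between-arm analysis for time since stroke.

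The cost is a wording amendment and one covariate. Table 1 lists medical history before allocation but does not name the onset date, so the sponsor must confirm that it is recorded for every patient and retrieve it where it is not.
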